### Withdrawal

If participants withdraw from the study before the end of the trial, the reason and date will be recorded. Participants who withdraw from the trial after 6 months of follow-up will be asked to have the final assessments at the 24-month follow-up. Outcomes assessed before the withdraw and at the 24-month follow-up will be used for the statistical analyses.

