### Randomization and blinding

To control for variation in study sites, the randomization will be stratified by the study sites. Participants in each site will be randomly assigned to the intervention arm or placebo arm in a ratio of 1:1 based on computer generated random numbers using block randomization (with a block size of 6). Participants, investigators, outcome assessors, as well as statisticians will be blinded to the group allocation in this trial. Allocation concealment will be ensured by keeping the allocation data confidential and using the visual- and taste-masked inert placebo. Emergency unblinding will be permissible when a serious adverse event happens. Participants who are unblinded will be withdrawn from the trial.

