### Sample size

The sample size calculations were performed using the formula: n_1_ = n_2_ = 2 × [(Z_α_ + Z_β_) × σ/δ]^2^ and assumed α = 0.025 (one-sided) and β = 0.20 (Z_α_ = 1.96; Z_β_ = 0.842).

According to a previous study, the standard deviation of annual tibiofemoral cartilage volume loss in obese knee OA patients was 1.92% (σ), and taking metformin could decrease the average annual tibiofemoral cartilage volume loss by 1.07% (δ) [22]. Considering that it may take a long time for metformin to exert the protective effect on articular cartilage, we assumed that the volume of articular cartilage begins to differ after 1 year of metformin use, that is, the second year of follow-up can be used to observe the effect of metformin on the articular cartilage volume. Based on the assumption and the data from the previous study, we calculated that 51 participants per group (n_1_, n_2_) are needed.

Sample size calculation was also performed based on another primary outcome, namely, WOMAC score. Up to now, no study has reported the effect of metformin on WOMAC score. We hypothesized that metformin treatment for 2 years will have more decrease in WOMAC score compared with placebo. The minimum clinically important difference (MCID) of WOMAC score in patients with knee OA was reported being 12, 14, 16, 18, and 20% of the baseline score [29–33]. Combined, we took the 16% for sample size calculation. In our previously established Chinese symptomatic knee OA cohort, the mean baseline WOMAC score was 99.95 (a total score of 240) [28]. Based on these data, it is estimated that the difference in the changes in WOMAC score (a total score of 2400) between metformin and placebo groups needs to be greater than 159.92 (δ) to achieve MCID. In our previous clinical trials for patients with knee OA, the standard deviation of change from baseline to two-years follow-up of WOMAC score was 413.74 (σ). Therefore, the sample size was calculated as 105 for each group (n_1_, n_2_).

Take into consideration of these two calculations and a 20% dropout over the trial, 131 participants in each arm will be sufficient to detect the differences of primary outcomes between the two groups.

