### Statistical analysis plan

Baseline characteristics will be reported per group using descriptive statistics (means, proportions, and medians as appropriate) without statistical tests.

The primary analyses will be intention-to-treat analyses of primary and secondary outcomes. Per-protocol analyses will be performed as the secondary analyses, and participants with an average daily dose of 0.5-2 g of the investigational drug will be included in the per-protocol analyses. Missing data caused by loss to follow-up and nonresponses will be addressed by multiple imputations with chained equations. Imputations will be performed separately for each treatment group and each outcome using baseline variables of age, sex, BMI, and study site and non-missing values of the outcomes at baseline and each follow-up with the assumption of data missing at random. The treatment effect will be analyzed using linear mixed effect models. In the models, baseline covariates (age, sex, BMI, baseline value of the corresponding outcome), treatment, month, and the interactions of covariates and treatment with month will be entered as fixed effects. The correlation within the study sites and the repeated measures will be addressed using trial site and participant identification as random intercepts. Month will be treated as random slope to allow different treatment effects among knee OA patients over time. Changes in outcome measures within each group and difference of the changes between groups from baseline to follow-up will be calculated using linear combinations of the estimated coefficients.

Pre-specified stratified analyses will be performed to explore whether BMI could affect the treatment effect of metformin on knee OA. This will be conducted by introducing a 3-way interaction between treatment, month, and BMI in the linear mixed-effects models.

Because of the potential for type I error due to multiple comparisons, the findings for the analyses of the secondary outcomes and the stratified analyses will be interpreted as exploratory. A 2-sided *P* value of 0.05 or less will be considered as statistically significant.

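### Month-24 outcomes are not sought from participants who withdraw in the first 6 months, so their values rest on by-arm missing-at-random imputation, which can overstate a real metformin effect

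*Protocol article*

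**What the plan says.** The Withdrawal section of the protocol article sets a cut-off for recall: "Participants who withdraw from the trial after 6 months of follow-up will be asked to have the final assessments at the 24-month follow-up". It says that outcomes obtained before withdrawal and at month 24 will be analysed. It states no request for those who leave sooner.

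Randomization and blinding permits emergency unblinding after a serious adverse event and adds: "Participants who are unblinded will be withdrawn from the trial".

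The Statistical analysis plan section states: "The primary analyses will be intention-to-treat analyses of primary and secondary outcomes". Missing outcomes are filled by multiple imputation with chained equations under missing at random, separately for each arm and each outcome. The predictors are age, sex, BMI, site and the outcome's own observed values.

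The section on assessment of knee structures, Table 1 and the Fig. 1 legend place MRI at baseline and month 24 only. WOMAC is collected at months 0, 3, 6, 12 and 24. The Intervention section escalates the dose over the first 4 weeks and lets the researchers reduce or stop the drug. It does not say whether stopping the drug ends follow-up.

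**The concern.** An intention-to-treat comparison is best supported by observed outcomes in everyone randomised, whatever happened to their treatment. The recall rule leaves month-24 outcomes unsought in the first 6 months. That window contains the whole dose escalation, which the Intervention section says is gradual in order to limit side effects. Treatment-related exits in this window are plausible, although the documents do not quantify them.

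The consequence differs between the co-primary outcomes. An early withdrawer has no post-baseline cartilage volume at all, so the imputation has only baseline variables to work with. For WOMAC there may be a month-3 value, possibly a month-6 value. In neither case does the listed imputation model include drug exposure or reason for leaving. The imputed values therefore follow same-arm participants who were observed, most of whom took the drug for longer.

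The Sample size section sharpens the point. It assumes that cartilage volume starts to diverge only after a year of metformin. On that assumption, a person who leaves before month 6 and takes no more metformin gains no cartilage benefit, yet by-arm imputation can credit them with the average benefit of those observed. A later analysis document cannot recover data that were never collected.

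**Working it through.** **Step 1. Reproduce the planned sample size.** Inputs are from the Sample size section: "assumed α = 0.025 (one-sided) and β = 0.20", that is Zα = 1.96 and Zβ = 0.842. This agrees with the analysis section: "A 2-sided *P* value of 0.05 or less will be considered as statistically significant".

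- Cartilage: "the standard deviation of annual tibiofemoral cartilage volume loss in obese knee OA patients was 1.92" (per cent) and "taking metformin could decrease the average annual tibiofemoral cartilage volume loss by 1.07" (per cent). n = 2 × [(1.96 + 0.842) × 1.92 / 1.07]² = 50.56, so 51 per arm.
- WOMAC: the difference "needs to be greater than 159.92", with SD of change 413.74. n = 2 × [(1.96 + 0.842) × 413.74 / 159.92]² = 105.10, given as 105 per arm.
- Dropout of 20%: 105 / 0.8 = 131.25, given as 131 per arm.

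The stated figures reproduce to within rounding. With 131 × 0.8 = 104.8 observed per arm, WOMAC power is 79.9%. The allowance therefore covers lost precision. It does nothing about bias.

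**Step 2. Size the possible bias.** The early-withdrawal rate is not in the documents, so these are assumptions:

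- d = share of the metformin arm that withdraws before month 6 and has no month-24 value.
- These people keep no drug benefit at month 24.
- By-arm imputation gives them, on average, the effect δ seen in observed metformin participants.
- δ is set to the planned values: 159.92 WOMAC points and 1.07% cartilage volume.
- Early withdrawers differ from the others only in the benefit lost.

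Then:

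- effect after imputation = δ
- effect in all randomised = (1 − d) × δ
- overstatement = d × δ, or 1/(1 − d) − 1 relative to the diluted effect

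| d | WOMAC effect, all randomised | Overstatement (points) | Relative to diluted effect | Cartilage effect, all randomised | WOMAC power, 131 per arm observed |
|---|---|---|---|---|---|
| 5% | 151.9 | 8.0 | 5% | 1.02% | 84.4% |
| 10% | 143.9 | 16.0 | 11% | 0.96% | 80.4% |
| 15% | 135.9 | 24.0 | 18% | 0.91% | 75.8% |
| 20% | 127.9 | 32.0 | 25% | 0.86% | 70.6% |

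Example for 10%: 0.90 × 159.92 = 143.9; 159.92 − 143.9 = 16.0; 16.0 / 143.9 = 11%. The 20% row is an outer case, in which the metformin arm's whole dropout allowance falls before month 6. The last column takes the diluted effect as true and everyone as observed; for comparison, power at the undiluted 159.92 with 131 per arm is 87.9%.

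**Step 3. What moves these figures.** If δ = 0, then d × δ = 0. Any retained benefit shrinks the overstatement in proportion. A month-3 WOMAC value can also pull the imputation towards the truth, so the WOMAC figures lie at the high end for a given d. The no-benefit assumption is firmest for cartilage, where it follows from the protocol's own delay of one year.

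**The case against.** The strongest reply is that the plan is less exposed than it looks, and much of that stands.

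- A reader might infer that the analysis loses early withdrawers. It does not. Imputation keeps them in the intention-to-treat set, and data obtained before withdrawal are used. What is lost is the observed month-24 value.
- A reader might infer that everyone who stops because of intolerance drops out of follow-up. The Intervention section allows a lower dose or stopping without saying that the participant leaves, and the Withdrawal section concerns leaving the trial. Some people off drug may stay under observation and so contribute to the same-arm values. The text does not promise this, however.
- A reader might infer that all unblinded participants are lost. Unblinding is permitted, not automatic, and the recall makes no exception for them. Those withdrawn after month 6 would be asked back, so only unblinding before then adds to the gap.
- A reader might infer that the plan is shown to be biased in favour of metformin. The documents give no withdrawal rate by arm or by time, only an overall 20% dropout. More early exits on metformin is an inference, and the calculation enlarges a real effect without creating one from nothing.

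Sensitivity analyses for missing data may also sit in a fuller plan that is not shown. They could show how much depends on the assumption, but could not replace the missing outcomes.

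**Conclusion.** The concern holds in a limited form. The recall rule leaves month-24 outcomes unsought from withdrawers before 6 months, including anyone unblinded in that time. Their contribution to both co-primary outcomes then rests on a by-arm missing-at-random assumption, and for cartilage volume on that assumption plus baseline data alone.

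If early withdrawal is related to treatment and metformin works, the effect can be overstated. The range of about 8 to 24 WOMAC points for 5% to 15% early withdrawal rests on an assumed rate, no retained benefit and a non-zero drug effect. It illustrates the possible size and is not an estimate for this trial. The defect is a stated rule that conflicts in spirit with the intention-to-treat label, and it is easily put right.

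**What to change.** - **Withdrawal:** remove the 6-month cut-off. Ask every randomised participant who has not withdrawn consent for follow-up to attend at least the month-24 WOMAC and MRI, whatever the time or reason for withdrawal.
- **Randomization and blinding:** replace withdrawal from the trial after unblinding with continued outcome follow-up under blinded assessment.
- **Intervention:** state that stopping study drug does not end follow-up.

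These changes concern outcome collection only and leave the rules on dosing, stopping of drug and emergency unblinding as they are. The planned 131 per arm is unchanged, and the month-24 visit and MRI are already scheduled for every participant. The cost is a short amendment and some extra effort to recall people who are off drug. It should be made before month-24 visits of early withdrawers are missed.

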### Data integrity and management

All data obtained will be kept strictly confidential and will be stored electronically on a database with secured and restricted access (Research Electronic Data Capture, REDCap). After each follow-up, the obtained data will be timely inputted into the electronic database. The entered data will be routinely checked to correct the potential mistaken input. The obtained MR images will be stored electronically and transferred to the sponsor (Guangzhou First People’s Hospital) in time. At the completion of the follow-up, the MR images will be uniformly assessed and the acquired data will be inputted into the electronic database at the primary site. Then, all the data will be checked and locked. After that, a two-step unblinding method will be applied. The first step of the unblinding will classify the participants to group A and group B for efficacy endpoints and safety analyses. When the analyses are completed, the second step of the unblinding will be conducted to assign group A and group B.

## Discussion

We have proposed a multicenter, randomized, double blind, and placebo-controlled trial to determine whether metformin intervention can modify knee structures and relieve knee symptoms in overweight knee OA patients. If metformin is proved to be effective on knee structures and symptoms, it will be a novel therapeutic approach to reduce knee OA progression.

Metformin is not just an antihyperglycemic drug but also has multiple health-protective effects [34, 35]. In vivo studies found that metformin had both structure-modifying and symptom-relieving effects in knee OA animal models [18–20]. Epidemiological studies also suggested a protective effect of metformin on OA [21, 22]. For the underlying mechanisms, studies suggested that the beneficial effect of metformin on OA could be mediated by protecting chondrocytes and inhibiting pain [18–20]. Also, it is reported that metformin could inhibit the inflammatory response in macrophages, while hyperinflammatory synovial macrophages exacerbate the progression of OA [36, 37]; therefore, metformin may exert OA-protective effect by modulating the inflammatory response of macrophages.

Obesity is an important risk factor for knee OA, as obesity increases not only the loading but also the pro-inflammatory adipokines, leading to mechanical damage as well as metabolic imbalances of the joint [38, 39]. Metformin has been shown to have a weight-losing effect [12], which could also explain the potential OA-protective effect. Our study found that metformin had a stronger protective effect against OA in obese OA mice than in OA mice with normal weight (not yet published). Therefore, overweight knee OA patients were selected in this trial as these knee OA patients are more likely to benefit from metformin intervention than those with normal weight. Besides, pre-specified analyses of interactions between BMI and metformin intervention on OA outcomes will be performed to explore if knee OA patients with higher BMI could benefit more from metformin intervention.

To assess OA progression, accurate measurement tools which could evaluate cartilage morphology and other structures of the joint are needed. Radiographic OA assessment is not responsive to a tangible change over a short interval, and as a two-dimensional assessment, it is highly vulnerable to measurement error because of issues such as variations in joint positioning [40]. MRI allows direct, accurate, and reliable assessment of joint structures, therefore offers a much better assessment for detecting knee OA progression [40, 41]. MRI assessment of cartilage morphology is now recommended as an endpoint for the evaluation of structure modification in trials of knee OA [41]. Therefore, cartilage volume as a continuous variable which can predict total knee replacement was selected as a co-primary outcome in this trial. Simultaneously, the WOMAC score which is the most commonly-used disease-specific outcome in OA [26] was selected as another co-primary outcome for the evaluating of OA symptoms. Thus, the findings from this study will show whether metformin intervention has both structure-modifying and symptom-relieving effects on knee OA. As for the secondary outcomes, structural changes including cartilage defects, effusion-synovitis, and bone marrow lesions are all predictive of total knee replacement [42–44], suggesting they are clinically relevant. VAS knee pain was also selected as a secondary outcome since it is thought to be the gold standard method for quantifying arthritic pain [45].

At present, knee OA is a major public health problem without effective therapeutics. Animal experiments and observational studies have suggested that metformin may have protective effects on knee OA. Based on these previous findings, this trial has been designed to determine whether metformin intervention can slow the progression and relieve the symptom of knee OA. If metformin is proved to be effective for knee OA, it will be used as a disease-modifying OA drug and therefore reduce the economic burden of the disease through improving the quality of life as well as reducing the need of joint replacement for knee OA patients.

## Data Availability

Not applicable.

## Abbreviations

ACR: American College of Rheumatology
AMPK: AMP-activated protein kinase
AQoL-4D: Four-dimensional Assessment of Quality of Life
BMI: Body mass index
CONSORT: Consolidated Standards of Reporting Trials
COX-2: Cyclooxygenase-2
DESS: Dual-echo in steady state
DMM: Destabilization of the medial meniscus
GDP: Gross domestic product
mTOR: Mammalian target of rapamycin
MR: Magnetic resonance
MRI: Magnetic resonance imaging
OA: Osteoarthritis
OARSI: Osteoarthritis Research Society International
PHQ-9: Nine-items Patient Health Questionnaire
SIRT1: Specifically silent information regulator 1
VAS: Visual analogue scale
WATSf: Water Selected fluid
WOMAC: Western Ontario and McMaster Universities Osteoarthritis Index
